## Abstract

**Introduction:**

This study is designed to determine whether a full randomised controlled
trial (RCT) examining the clinical effectiveness and safety of total knee
replacement surgery with or without a tourniquet is warranted and
feasible.

**Method and analysis:**

Single centre, patient-blinded and assessor-blinded RCT. A computer-generated
randomisation service will allocate 50 participants into one of two trial
treatments, surgery with or without a tourniquet. The primary objective is
to estimate recruitment, crossovers and follow-up of patients. All patients
will have an MRI scan of their brain preoperatively and day 1 or 2
postoperatively to identify ischaemic cerebral emboli (primary clinical
outcome). Oxford Cognitive Screen, Montreal Cognitive Assessment and
Mini-Mental State Examination will be evaluated as outcome tools for
measuring cognitive impairment at days 1, 2 and 7 postoperatively. Thigh
pain, blood transfusion requirements, venous thromboembolism, revision
surgery, surgical complications, mortality and Oxford knee and five-level
EuroQol-5D scores will be collected over 12 months.
*Integrated qualitative research study*: 30 trial
patients and 20 knee surgeons will take part in semistructured interviews.
Interviews will capture views regarding the pilot trial and explore barriers
and potential solutions to a full trial. *Multicentre cohort
study*: UK National Joint Registry data will be linked to
Hospital Episode Statistics to estimate the relationship between tourniquet
use and venous thromboembolic event, length of hospital stay, risk of
revision surgery and death. The study will conclude with a multidisciplinary
workshop to reach a consensus on whether a full trial is warranted and
feasible.

**Ethics and dissemination:**

National Research Ethics Committee (West Midlands-Edgbaston) approved this
study on 27 January 2016 (15/WM/0455). The study is sponsored by University
of Warwick and University Hospitals Coventry and Warwickshire. The results
will be disseminated via high-impact peer-reviewed publication.

**Trial registration number:**

ISRCTN20873088;
Pre-results.

Strengths and limitations of this studyComprehensive feasibility research.Clearly defined outcome measures.Patient blinding.Single-centre design with small sample size.Absence of blinding among clinicians delivering the intervention.

## Introduction

Arthritis of the knee can cause pain and restrict activities of daily living. Total
knee replacement (TKR) surgery is a surgical procedure aimed at resolving the
symptoms of end-stage knee arthritis.^1^ TKR
surgery is typically undertaken with the aid of a tourniquet. A tourniquet acts as
an occlusive device around the thigh with the aim of reducing blood flow distally.
In the UK, over 90% of TKRs are performed with a tourniquet.^2 3^ Anecdotally, surgeons believe using a tourniquet provides
a bloodless field to improve the operative field of view.^4^ Many surgeons also believe using a tourniquet improves the
quality of the cementation of the knee implants^5^ by reducing bone bleeding and allowing better interdigitation of the
cement into the porous bone.

Previous systematic reviews have concluded that the use of tourniquets did not reduce
intraoperative or postoperative blood loss^6^
and were associated with significant complications including venous thromboembolic
events (VTEs),^5^ wound infection, bruising and
nerve palsy.^5 7^

In TKR surgery, a tourniquet causes both arterial and venous stasis for the duration
it is applied. It is therefore unsurprising that the use of a thigh tourniquet might
increase the risk of postoperative VTE.^2^
However, VTE may not be the only thromboembolic risk associated with using a
tourniquet. Research has demonstrated that systemic emboli can occur when the
tourniquet is deflated with up to a 60% prevalence of echogenic material in
the circle of Willis.^8 9^ Emboli may reach
the systemic circulation through the pulmonary capillaries or the opening of other
pulmonary vessels.^9^ The prevalence of
postoperative cognitive impairment after TKR is high with reports in the literature
varying from 41%–75% at 7 days to 18%–45% at 3 months,
and this may in part be explained by cerebral emboli if they are occurring following
the release of a tourniquet.^10^

Although studies have demonstrated that tourniquets do not substantially reduce blood
loss and may increase complications, a review of these studies, by Alcelik
*et al*
7, identified significant design flaws,
including issues with randomisation, blinding and the absence of clearly defined
outcome measures. Furthermore, no controlled studies have addressed or quantified
one of the most potentially serious risks associated with tourniquet, which are
cerebral emboli, and any resultant cognitive impairment.

There may be problems with running a trial that involves recruiting patients who,
once it is explained, may not be prepared to accept the potential risks of surgery
with a tourniquet. Equally, surgeons may be not willing to change surgical practice
for a randomised trial.

We designed a feasibility study, which includes three separate but integrated
projects: (A) pilot randomised controlled trial (RCT), (B) integrated qualitative
research study and (C) retrospective multicentre cohort study.

The objective of the safety and feasiblity evaluation of tourniquets for total knee
replacement surgery (SAFE-TKR) study is to establish whether a full
RCT evaluating tourniquets in knee replacement surgery is warranted and
feasible.

## Pilot RCT

The primary objective of the pilot trial is to estimate recruitment, crossover and
follow-up of patients for a full trial.

### Secondary objectives

evaluate MRI for detecting postoperative ischaemic cerebral emboli,
including an estimate of the size and direction of any effect;evaluate tools for detecting postoperative cognitive impairment. These
tools include Mini-Mental State Examination (MMSE), Montreal Cognitive
Assessment (MoCA) and the Oxford Cognitive Screen (OCS), including an
estimate of the size and direction of any effect;evaluate other candidate primary/coprimary/secondary outcome measures for
assessment within a larger trial including: thigh pain, symptomatic VTE,
mortality, revision surgery, blood transfusion requirements, function
and health-related quality of life. To include obtaining estimates for
the SD of continuous outcome variables and differences in proportions
for categorical outcome variables in order to facilitate potential
sample size calculations for a full trial;test and optimise patient information material and the patient pathway
for a full trial.

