#### Randomisation

All patients who consent to the trial will be registered and then undergo a
preoperative MRI of their brain. Patients will be allocated 1:1 via Warwick
randomisation service (independent of the study team) to either TKR surgery
with tourniquet or TKR surgery without tourniquet using minimisation to
ensure balance between the treatment arms as regards patients with a history
of VTE.^13^ To ensure allocation
concealment, following enrolment patient details are entered on a web-based
form, and the treatment allocation are generated.

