### Sample size calculation

As this is a pilot trial and not designed to measure effect, a formal sample size
calculation is not required (the statistical analysis will be largely
descriptive). We propose seeking to recruit and obtain primary clinical outcome
data for 50 patients for descriptive analysis.

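### Between-arm differences in proportions from about 25 patients per arm are named as an input to the full trial's sample size, for which they are too imprecise

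*Protocol article*

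**What the plan says.** The third secondary objective of the pilot RCT concerns candidate outcomes for a larger trial: thigh pain, symptomatic VTE, mortality, revision, transfusion, function and quality of life. For these it seeks SDs where the outcome is continuous and, otherwise, "differences in proportions for categorical outcome variables in order to facilitate potential sample size calculations for a full trial". The first two objectives, on MRI lesions and cognitive tools, also ask for an "estimate of the size and direction of any effect", but do not mention sample size.

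The Sample size calculation section opens "As this is a pilot trial and not designed to measure effect", concludes that no formal calculation is needed, and aims for primary clinical outcome "data for 50 patients for descriptive analysis". Under Randomisation, "Patients will be allocated 1:1 via Warwick" randomisation service, which gives about 25 per arm. The article does not print that figure.

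Two other places bear on the point. The Multicentre cohort study will estimate group differences in mortality and VTE to 12 months and in revision at 1, 5 and 10 years; its Statistical Analysis section says these results will inform planning of a full trial. The Conclusions section puts pilot, cohort, published and, where applicable, pooled data before a consensus workshop, and its feasibility conditions contain no effect-size threshold.

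**The concern.** The objective treats the two types of outcome differently. For a continuous outcome it takes the SD, a nuisance parameter that a pilot can reasonably supply. The counterpart for a binary outcome is the event proportion in one arm or overall. The objective names the between-arm difference instead, which is the treatment effect, and the Sample size calculation section says the pilot is not built to measure that.

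The size of a two-arm trial varies with the inverse square of the target difference, so error in a difference observed in 25 per arm is greatly magnified in the computed size. If the observed difference is used as the target, or pulls the target towards itself, a chance large difference gives an underpowered full trial and a chance small one gives an inflated or unworkable size. For rare candidates such as VTE, revision and death, the observed difference will often be zero or rest on a single event. Planning a full trial is what this study is for, so the quality of this input matters even though the pilot's own conduct is unaffected.

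**Working it through.** **Nothing to reproduce.** The article gives no alpha, power, event rate or precision target behind the figure of 50. The check is how precise a difference from this pilot would be, and what follows if it is used to size the full trial.

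**Inputs from the article.** 50 patients, 1:1, so n = 25 per arm.

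**Assumptions, since the article gives none.** Two-sided 5% test, 90% power, 1:1 allocation in the full trial, and the true rates shown below.

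**Formulas.**
- Standard error of the observed difference: SE = √[(p₁q₁ + p₂q₂)/25], with q = 1 − p.
- Size per arm (unpooled normal): N = (1.960 + 1.282)² × (p₁q₁ + p₂q₂)/(p₁ − p₂)² = 10.507 × (p₁q₁ + p₂q₂)/(p₁ − p₂)².
- Every pair of pilot counts (0–25 in each arm) is weighted by its exact binomial probability. N is computed from the observed proportions whenever the difference has the right sign, and the power of a trial of that size is then evaluated at the true rates.

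**Case 1: true rates 20% v 10%.**
- SE = √[(0.16 + 0.09)/25] = 0.10, so the observed difference has a 95% range of 10 ± 19.6 points, about −10 to +30.
- Correct N = 10.507 × 0.25/0.01 = 263 per arm.
- Probability of a zero or reversed difference: 21%.
- Otherwise the 10th to 90th percentile of N is about 44 to 1,576 per arm.
- Of trials sized this way, 56% have power below 80%.

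The two percentiles match ordinary pilot results:
- 7 v 1 events: 10.507 × (0.2016 + 0.0384)/0.24² = 44 per arm.
- 4 v 3 events: 10.507 × (0.1344 + 0.1056)/0.04² = 1,576 per arm.

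**Case 2: true rates 40% v 20%.**
- SE = √[(0.24 + 0.16)/25] = 0.126.
- Correct N = 10.507 × 0.40/0.04 = about 105 per arm.
- Probability of a zero or reversed difference: 8%.
- Otherwise N runs from 28 to 657 per arm (10th to 90th percentile), and 45% of trials so sized have power below 80%.

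**Case 3: rare outcomes.**
- At an assumed 2%, the chance of no events in an arm is 0.98²⁵ = 60%, and in the whole pilot 0.98⁵⁰ = 36%.
- Zero events in 25 still leaves an exact upper 95% limit for that arm of 1 − 0.025^(1/25) = 13.7%.
- At 2% v 1%, about 3,100 per arm would be needed. The chance of a zero or reversed difference is 67%, and a result of 1 v 0 events would suggest 10.507 × 0.0384/0.0016 = 252 per arm.

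**Sensitivity to method.** With the pooled-variance formula, and with zero and reversed results kept in (no finite N when the counts are equal), the ranges widen: 47 to 2,525 per arm at 20% v 10% (correct 266) and 32 to 2,252 at 40% v 20% (correct 109). The conclusion does not depend on the formula.

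**The case against.** The strongest reply is that the article prescribes no plug-in rule. It says the estimates are to facilitate potential calculations, which makes the difference one input; the enumeration models mechanical use that nobody has promised. This stands as a limit on how certain the harm is. It does not make the difference a good input, and the article names no other source for the target difference on these outcomes, such as clinical importance.

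Second, the article already provides a better source for rare events. The registry cohort covers VTE, mortality and revision, is said to inform full-trial planning, and goes to the workshop with published data. This also stands, and it means the rare-event figures do not describe the only evidence the planners will have. The objective should say so, because as worded it draws those same outcomes from the pilot.

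Third, describing a difference is compatible with a largely descriptive pilot. That is correct. The tension with the Sample size calculation section lies in the stated purpose, and reporting a difference is unobjectionable.

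Fourth, the assumed rates are not the article's. 40% v 20% may bring MRI lesion rates to mind, and those fall under a different objective that does not mention sample size. Both pairs of rates should be read as illustrations of how a binary outcome behaves with 25 per arm.

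A reader might also infer that an unlucky pilot would lead to the full trial being wrongly abandoned. The Conclusions section does not support this: its conditions concern recruitment, surgeon willingness, a usable outcome measure and stakeholder consensus, with no effect-size criterion. An unworkable computed size could at most weigh indirectly in the workshop.

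**Conclusion.** The point holds in a limited form. A secondary objective names an observed treatment effect as a sample size input, while the article elsewhere says the pilot is not designed to measure effect. At 25 per arm such a difference is too imprecise to set or inform a target difference. If it were used that way, about half of the resulting trials would fall below 80% power (45% at 40% v 20%, 56% at 20% v 10%, given a difference in the right direction), and the computed sizes would span more than a twentyfold range.

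These figures rest on the assumed rates, 90% power and direct use of the observed difference. The article commits to none of these, so they show what is at risk and do not predict what will happen. The consequence at issue is a mis-sized full trial. No stated feasibility criterion is breached, and the pilot's primary objective is untouched. Estimating SDs for continuous outcomes is sound and is not criticised here. The wording should be corrected before the pilot's results are used for planning.

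**What to change.** In the third secondary objective of the pilot RCT:
- Replace differences in proportions with the proportion in the standard-practice arm and the overall proportion, each with a 95% confidence interval. On the Introduction's figure of over 90% tourniquet use in the UK, the standard-practice arm is the tourniquet arm.
- State that the full trial's target difference will be set on clinical importance, for example at the consensus workshop, and not on the pilot's observed difference.
- State that VTE, revision and mortality rates for sizing come from the linked registry and hospital-episode cohort, in line with that study's own Method and Statistical Analysis sections.
- Label any observed between-arm difference as descriptive, so that the objective agrees with the Sample size calculation section.

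This is a change of wording and needs no extra patients or data. The possible downside is a larger planned full trial than a favourable pilot difference would have suggested.

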### Method

The protocol was produced in accordance with the Standard Protocol Items:
Recommendations for Interventional Trials guidelines.^11^ The trial will be reported in line with the Consolidated
Standards of Reporting Trials (CONSORT) statement.^12^

A single-centre two-arm pilot RCT will be performed. All patients under the care
of 13 participating orthopaedic consultants at University Hospital Coventry and
Warwickshire National Health Service (NHS) trust are potentially eligible for
entry into the trial. The following eligibility criteria will be implemented for
patient selection:

#### Inclusion criteria

undergoing a primary unilateral TKRage ≥18 yearsable to give written informed consent and to participate fully in the
interventions and follow-up procedures.

#### Exclusion criteria

Patients for whom MRI is contraindicated due to:non-compliant heart pacemaker or defibrillatornon-compliant metallic foreign body, for example, in one
or both eyes and aneurysm clips in the brainclaustrophobia (eg, difficulty in an elevator or
telephone box).Patients not suitable for a thigh tourniquet (eg, peripheral vascular
disease).Previous participation in the SAFE-TKR study.

Patients already scheduled for TKR surgery will be screened based on the
eligibility criteria. A trained research associate will contact potentially
eligible patients via telephone. Patients who are interested in taking part
in the study will then be sent a patient information sheet and consent form
and a date arranged to answer any further questions about the study and take
consent. Verbal consent will initially be taken, followed by signed written
consent via post or in person depending on the patient’s preference
(see online supplementary appendix 1 and 2).

#### Randomisation

All patients who consent to the trial will be registered and then undergo a
preoperative MRI of their brain. Patients will be allocated 1:1 via Warwick
randomisation service (independent of the study team) to either TKR surgery
with tourniquet or TKR surgery without tourniquet using minimisation to
ensure balance between the treatment arms as regards patients with a history
of VTE.^13^ To ensure allocation
concealment, following enrolment patient details are entered on a web-based
form, and the treatment allocation are generated.

#### Planned intervention

Patients will undergo routine elective primary unilateral TKR (cemented)
using the standard technique of the anaesthetist and the operating surgeon.
Both groups will have a thigh tourniquet applied to the relevant lower limb.
Once the patient is fully anaesthetised, one of the following interventions
will be applied:

##### Group A (tourniquet inflated)

The tourniquet will be inflated prior to the surgeon creating a wound,
and only deflated once the procedure is deemed completed by the surgeon
(at a minimum this will be after all the TKR components have been
finally inserted).

##### Group B (tourniquet not inflated)

The tourniquet will not be inflated during the procedure.

In line with National Institute for Health and Care Excellence (NICE)
guidance, all patients will receive the following routine chemical and
mechanical VTE prophylaxis:intermittent pneumatic calf compression until
patient’s mobility is no longer significantly
reducedlow molecular weight heparin (or unfractionated heparin for
patients with severe renal impairment or established renal
failure), started 6–12 hours after surgery and
continued for 14 days postoperatively.

#### Clinical outcomes and time points

**Table 1 T1:** Clinical outcomes and time points

Time point	Data collection
Baseline	Demographics, total volume of acute brain lesions, MMSE, MoCA, OCS, OKS, EQ-5D-5L, VAS and haemoglobin level.
Day 1	Total volume of acute brain lesions, MMSE, MoCA, OCS, VAS and haemoglobin level.
Day 2	Total volume of acute brain lesions (if not done on day 1), MMSE, MoCA, OCS, VAS and haemoglobin level (if not done on day 1).
Week 1	MMSE, MoCA, OCS, VAS, OKS, EQ-5D, number of intraoperative/postoperative blood transfusions until discharge and surgical complications.
6 months	OKS, EQ-5D and surgical complications.
12 months	OKS, EQ-5D-5L, number of symptomatic VTEs, surgical complications, revision rate and all cause mortality.

Data will be obtained from next of kin and healthcare
records.

EQ-5D-5L, five-level EuroQol-5D; MMSE, Mini-Mental State
Examination; MoCA, Montreal Cognitive Assessment; OCS, Oxford
Cognitive Screen; OKS, Oxford Knee Score; VAS, visual analogue
scale; VTEs, venous thromboembolic events.

##### Primary clinical outcome

The primary clinical outcome will be evidence of new acute ischaemic
brain lesions on MRI. The total number and volume of acute brain lesions
detected on MRI per patient will be recorded. Presurgery MRIs will be
obtained no more than 60 days before surgery, and
postsurgery MRIs will be obtained up to 2 days after surgery.
Diffuse-weighted MRI is the most powerful tool for diagnosing acute
ischaemic brain lesion caused by cerebral microembolism providing high
level of sensitivity and specificity.^14–16^ The MRIs will all follow a
standardised protocol including fast spin-echo fluid-attenuated
inversion recovery sequences and diffusion-weighted spin
echo-echo planar imaging. The diffusion-weighted sequence will consist
of an initial T2-weighted acquisition followed by a second acquisition
with the application of diffusion-sensitising gradients in the three
orthogonal directions. Lesions will also be described according to the
vascular territory (anterior, middle, posterior cerebral arteries or
vertebrobasilar arteries), side and type (cortical vs subcortical or
deep grey matter). A planimetry of each lesion will be performed by
using a grid overlay (using Image Processing and Analysis in Java
software, National Institutes of Health) and by calculating
lesion volume by multiplying the number of involved grids by the slice
thickness and slice gap. Attack rate (presence of new lesions/number of
patients) will also be calculated. A new lesion will be defined as a
focal hyperintense area detected by the fluid-attenuated inversion
recovery sequence, corresponding to a restricted diffusion signal in the
diffusion-weighted imaging sequence.^17^ Scans will be read and evaluated by two experienced
consultant radiologists blinded to the timing of the imaging, allocated
intervention and the neurological status of the patient. Even
asymptomatic cerebral emboli, which may be detected using this approach,
are associated with gradual memory impairment and cognitive
decline.^18–20^

##### Secondary outcomes

MoCA preoperatively and days 1, 2 and 1 week
postoperatively: the MoCA is a brief cognitive screening
tool with high sensitivity and specificity for detecting mild
cognitive impairment.^21^OCS preoperatively and days 1, 2 and 1 week
postoperatively: the OCS has higher sensitivity than the
MOCA for measuring cognitive deficits associated with stroke
(spatial disorders and apraxia), and it provides response
speed as well as accuracy measures, so that indices such as
processing speed can be derived.^22^MMSE scores preoperatively and days 1, 2 and 1 week
postoperatively: the MMSE is the most commonly used tool
for measuring cognitive impairment and has been used extensively
to measure disturbances in postoperative cognition.^23–25^Acute thigh pain preoperatively and on days 1, 2 and
1 week postoperatively: the 100 mm visual
analogue scale (VAS) with 0 being no pain and 100 mm
being the worst pain is a validated patient-reported outcome
measure for pain following TKR surgery.^26^Oxford Knee Score (OKS) preoperatively and at 1 week, 6
and 12 months postoperatively: this is a
self-administered, validated knee replacement composite outcome
measure of knee pain and function consisting of 12 items. The
score ranges from 12 to 60, where 12 represents the best outcome
and 60 represents the worst outcome.^27^Five-level EuroQol-5D (EQ-5D-5L) scores preoperatively and at
1 week, six and 12 months
postoperatively: This is a validated measure of
health-related quality of life, consisting of a five-dimension
health status classification system and a separate VAS. EQ-5D-5L
is primarily designed for self-completion by respondents and
suited for use in postal surveys, in clinics and face-to-face
interviews. It is cognitively simple, taking only a few minutes
to complete.^28 29^Number of symptomatic VTE events up to 12 months
postoperatively: symptomatic VTE events will be defined
based on NICE guidance: deep vein thrombosis=swollen or
painful leg and a positive proximal leg vein ultrasound scan;
pulmonary embolism=chest pain, shortness of breath or
haemoptysis and positive CT pulmonary angiogram (CTPA) scan or
ventilation perfusion single photon emission computed tomography
(V/Q SPECT) or planar scan if CTPA not available. Symptomatic
VTEs will be captured throughout the postoperative period via
hospital records. In addition, patient questionnaires at 6 and
12 months will capture further data.Surgical complications up to 12 months
postoperatively: patient questionnaires and healthcare
records will collect adverse events (AEs) that are deemed
to be as a direct result of surgery. Two blinded researchers
will determine whether AEs should be classified as a surgical
complication, where there is disagreement, a third researcher
will determine the final allocation.Number of intraoperative/postoperative blood transfusions until
discharge: data will be obtained from hospital records
and recorded as number of units transfused.Change in haemoglobin concentration (Hb g/L): routinely
collected haemoglobin concentrations (Hb g/L) measured from a
full blood count taken on days 1–3 postoperatively (the
sample closest to day 1 will be favoured) will be subtracted
from a preoperative (Hb g/L) measured within 3 months
(the sample closest to the date of surgery will be
favoured).Revision rate of the TKR prosthesis at
12 months: revision of the prosthesis for any
reason will be established by patient questionnaires at
12 months and hospital records.All-cause mortality rates at 12 months: all
baseline data will be summarised descriptively by intervention
group. The flow of patients through the trial will be presented
in a CONSORT diagram, and patients withdrawn
are summarised by treatment group.

